## Abstract

**Objectives::**

The available evidence shows that hypoxemia after Stanford Type-A acute aortic dissection (AAD) surgery is a frequent cause of several adverse consequences. The pathogenesis of postoperative hypoxemia after AAD surgery is complex, and ischemia/reperfusion and inflammation are likely to be underlying risk factors. Xenon, recognized as an ideal anesthetic and anti-inflammatory treatment, might be a possible treatment for these adverse effects.

**Methods/Design::**

The trial is a prospective, double-blind, 4-group, parallel, randomized controlled, a signal-center clinical trial. We will recruit 160 adult patients undergoing Stanford type-A AAD surgery. Patients will be allocated a study number and will be randomized on a 1:1:1:1 basis to receive 1 of the 3 treatment options (pulmonary inflated with 50% xenon, 75% xenon, or 100% xenon) or no treatment (control group, pulmonary inflated with 50% nitrogen). The aims of this study are to clarify the lung protection capability of xenon and its possible mechanisms in patients undergoing the Stanford type-A AAD surgery.

**Discussion::**

This trial uses an innovative design to account for the xenon effects of postoperative oxygen impairment, and it also delineates the mechanism for any benefit from xenon. The investigational xenon group is considered a treatment intervention, as it includes 3 groups of pulmonary static inflation with 50%, 75%, and 100% xenon. It is suggested that future trials might define an appropriate concentration of xenon for the best practice intervention.

KEY POINTSThis is the first randomized-controlled trial assessing xenon protection against postoperative oxygen impairment in adults undergoing Stanford Type-A acute aortic dissection surgery.This study will determine the potential of different concentration of xenon-treatment against postoperative oxygen impairment in adults undergoing Stanford Type-A acute aortic dissection surgery.This study will determine pathophysiological mechanisms of xenon-treatment on postoperative acute oxygen impairment.This study will conducted in the largest aortic medicine clinic center of China and large nationally representative sample of the general population in China was collected. However, this is a single-center study; therefore, the applicability of the results to other medical center would be affected and a multicenter large cohort study is recommended.

## Introduction

1

Acute aortic dissection (AAD) is a severe cardiovascular disease demonstrating the characteristics of acute onset and rapid development, with high morbidity and mortality.^[1]^ Previous work by Wang et al^[2]^ showed that the incidence of postoperative hypoxemia is up to 49.5% in adult patients undergoing Stanford A AAD surgery. Postoperative hypoxemia was always related with postoperative acute lung injury (ALI), even acute respiratory distress syndrome (ARDS) according to the “Berlin criteria” of 2012 by the European Society of Intensive Care Medicine.^[3]^ The pathogenesis of hypoxemia after AAD surgery is complex and remains unknown. However, studies have indicated that ischemia/reperfusion and inflammation are likely to be underlying risk factors.^[4–6]^ Therefore, reducing inflammation might be a potential therapeutic strategy for treating postoperative hypoxemia.

Xenon has been recognized as an ideal anesthetic for its hemodynamic stability and anti-inflammatory effects.^[7–9]^ In recent years, it has also been demonstrated to have neuroprotective and cardioprotective effects by inhibiting inflammation in different models subjected to preconditioning, real-time conditioning, and postconditioning.^[10–13]^ However, the effects of xenon on respiratory function in patients with Stanford type A AAD during cardiopulmonary bypass (CPB) with deep hypothermic circulatory arrest (DHCA) remain unclear. In addition, no RCTs have been performed on patients with postoperative oxygen impairment to show that xenon treatment is more effective than inhaled oxygen.

## Methods/design

2

### Ethical approval

2.1

Ethical approval was obtained on March 10, 2016, from the Beijing Anzhen Hospital Clinical Research Ethics Committee (2016006). The study has been accepted on to the Beijing municipal science and technology plan project. Personal information about potential and enrolled participants will be collected, shared, and maintained by sponsor in order to protect confidentiality before, during, and after the trial.

### Design of trial

2.2

The trial is a 4-group, parallel, RCT, which has been registered at www.clinicaltrials.gov (Identifier: NCT02468531). By performing 4 2-way comparisons, we will test differences between groups. Patients will be randomized in a 1:1:1:1 ratio. Blinding will be performed for patients, post intervention assessors, statisticians, and investigators.

The null hypothesis for this trial is that there is no difference in protection effects between nitrogen and xenon in patients with postoperative oxygen impairment. The patients who receive nitrogen are the control group in this comparison. If this null hypothesis is rejected, then inhaled xenon may be an effective treatment. If this null hypothesis is not rejected, then inhaled xenon may be ineffective.

However, there is also a need to understand how potential treatment differences are achieved, and/or if different concentrations of inhaled xenon produce similar effects. Further comparisons, including the use of a control intervention, can provide this information.

### Aims

2.3

The aims of this study are to clarify the lung protection effects of xenon and its possible mechanisms in patients undergoing the Stanford type-A AAD surgery. It includes a detailed statistical analysis of perioperative clinical baselines and serum variables, such as coagulation, fibrinolysis, inflammatory, reactive oxygen species, and endothelial cell function. The outcomes of this study will detail the differences in postoperative oxygen impairment between the control group and xenon groups, and pathophysiological mechanisms of xenon, which will be beneficial for the prophylaxis, and/or treatment of postoperative acute lung injury.

### Primary and secondary outcome measures

2.4

#### Primary outcome measure

2.4.1

The study primary outcome measure is the perioperative change of the patient's oxygenation index (OI) presurgery, at end of surgery, and at 6 hours postsurgery. The oxygenation index is calculated by the arterial oxygen tension (PaO_2_)/inspired oxygen fraction (FiO_2_) ratio, and is a validated and effective measure of oxygen impairment change.

#### Secondary outcome measures

2.4.2

The following are the secondary outcome measures: inflammatory cytokines and reactive oxygen species (ROS) presurgery, at end of surgery, at 6 and 24 hours postsurgery; extubation time; and complications. The timing of all assessments is shown in Table 1 as a schedule of events.

**Table 1 T1:**

Timetable of assessments.

### Study participants

2.5

The diagnosis of AAD will be confirmed in all patients by a consultant surgeon. A clinical history and clinical examination will be completed by recruiting surgeons on the team. Dissection is considered AAD if the time from the onset of the symptoms to surgery is 14 days or less. This study will include only type A AAD, as according to the Stanford classification.^[14,15]^

#### Inclusion criteria

2.5.1

Patients diagnosed with Stanford type A AAD by consultant's clinical judgment using local methods of diagnosis, which include clinical history, chest radiography (x-rays), transthoracic ultrasound, and contrast-enhanced computed tomography (CT), or magnetic resonance imaging (MRI) will be included. Patients aged 18 to 65 years old, and patients eligible for AAD surgery will be included, as well.

#### Exclusion criteria

2.5.2

A participant will not be enrolled into the study if any of the following conditions apply: coronary heart disease, heart failure, severe cardiac tamponade, unstable hemodynamics, severe nervous system abnormalities, clinically apparent malperfusion including lower limb, cerebral, coronary and renal malperfusion, and visceral ischemia or severe hepatic and renal abnormalities. Patients will also be excluded if they have undergone any cardiac and thoracic surgeries, are unlikely to be able to perform the required clinical assessment tasks, have significant cognitive impairment or language issues, are unable to provide consent to participate in the study or have been prescribed non-steroidal anti-inflammatory drugs or corticosteroids before or after hospital admission

### Study procedures

2.6

#### Recruitment organization

2.6.1

Patients considered for AAD will be identified in the emergency department. In all cases, the consultant cardiac surgeon will have final approval of a patient's eligibility for the study. Patients will be provided with written information about the study and asked to opt in. If their interest continues, they will be provided with further written information and evaluated for assessment and consent.

#### Randomization

2.6.2

After written informed consent is obtained and patient eligibility confirmed, patients will have a baseline assessment. They will then be randomized into the study. Patients will be given a study number and randomized on a 1:1:1:1 basis to receive 1 of the 3 treatment options or no treatment (control group). Randomization will be performed using an automated, computer-generated randomized digital table to ensure that all 4 groups are well balanced for the patient characteristics.

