#### Target sample size

3.4.1

A total sample size of 160 patients is planned. For a balanced 4-group trial, approximately 40 patients must be recruited per allocation group (nitrogen group, 50% xenon group, 75% xenon group, and 100% xenon group).

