#### Sample size calculation

3.4.2

The sample size calculation is based on the primary outcome measure, which is the variable of OI at perioperative period. Currently, there is no established minimal clinically important difference (MCID) for the OI. Based on previous study,^[17]^ an approximation to the MCID could be viewed as 38 mm Hg, the standard deviation (SD) of a single OI observation as 70 mm Hg, and the auto-correlation as 0.5. With a 5% (2-sided) type I error rate, based on preliminary experiments, 36 patients per treatment group are necessary, and the power was 0.80048. Assuming a 10% dropout rate, the final sample size will be 160 patients (40 patients/group) (Table 2). (Power Analysis and Sample Size, PASS V11.0, NCSS, LLC; Kaysville, UT).

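### A random digit table is said to ensure balance on patient characteristics, which it gives only in expectation; presurgery OI should be a covariate, not one of three outcome times

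*Protocol article*

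**What the plan says.** Section 2.6.2 (Randomization) of the protocol article states that patients will be "randomized on a 1:1:1:1 basis to receive 1 of the 3 treatment options or no treatment (control group"), and that this is done with a "computer-generated randomized digital table to ensure that all 4 groups are well balanced for the patient characteristics". It names no stratification or minimisation factor.

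Section 2.4.1 defines the primary outcome as the perioperative change in OI, measured before surgery, at the end of surgery and 6 hours afterwards. Section 3.4.3 (Analysis of endpoints) assigns OI to a repeated-measures analysis of variance and mentions no covariate. It also says that baseline data will be compared to see whether clinically important differences between the groups have arisen by chance.

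The sample size section (3.4.2) gives three planning values. The target difference is 38 mm Hg, offered as an approximate minimal important difference. The spread is stated as "the standard deviation (SD) of a single OI observation as 70 mm Hg". The correlation between repeated measurements is set at 0.5.

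**The concern.** A random digit table does not ensure balance on any measured characteristic. It makes the expected values equal across arms and leaves the realised values to chance. Blocking would equalise numbers, not characteristics. The statement in 2.6.2 is therefore wrong as written, and it conflicts with 3.4.3, which allows for chance differences.

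The claim matters most for presurgery OI, which is correlated with the later OI values and is also counted among the outcome measurements. A team that believes balance is assured has no reason to adjust for it. If a chance gap then appears, its effect on the comparison depends on how the repeated measurements are combined, which the text does not fix. Precision is also lost, because a measurement already collected is not used to explain variation in the postoperative values.

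**Working it through.** **Inputs.** Target difference 38 mm Hg, SD 70 mm Hg, correlation 0.5, two-sided 5%, 36 evaluable per arm, 40 recruited per arm (3.4.2); three OI time points (2.4.1). I assume that the SD is the same at every time point and that the correlation is 0.5 between every pair.

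**1. The plan's own sample size.** Averaging three equally correlated measurements gives:
- effective SD = 70 × √((1 + 2 × 0.5)/3) = 57.15
- SE with 36 per arm = 57.15 × √(2/36) = 13.47
- 38/13.47 = 2.82, so power is 0.805 (normal) or 0.794 (t), against the stated 0.80048
- 36/0.9 = 40 per arm, 160 in total

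So 36 is reproduced when all three times, presurgery included, are averaged. Other readings give 33 (correlation decaying with time), 40 (two measurements) or 54 (one). This suggests that presurgery OI was counted as an outcome in the calculation too.

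**2. Size of chance gaps in presurgery OI, 40 per arm.**
- SE of a two-arm difference = 70 × √(2/40) = 15.65; 95% range ±1.96 × 15.65 = ±30.7 mm Hg
- One given pair: 19/15.65 = 1.21, so P(gap > 19) = 22%; 38/15.65 = 2.43, so P(gap > 38) = 1.5%
- At least one of three xenon arms against the shared control (simulation): P(gap > 19) = 48%; P(gap > 38) = 4%

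The last two figures are the same, after rounding, if arm sizes vary at random around 40.

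**3. What a 19 mm Hg gap does when there is no treatment effect.** With correlation 0.5, the expected gap at each postoperative time is 0.5 × 19 = 9.5 mm Hg. The expected error in the comparison is then:

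| Contrast | Arithmetic | Error (mm Hg) |
|---|---|---|
| Mean of all three times | (19 + 9.5 + 9.5)/3 | 12.7 |
| Mean of the two postoperative times | 9.5 | 9.5 |
| Postoperative mean minus presurgery | 9.5 − 19 | −9.5 |
| Postoperative mean, presurgery as covariate | 9.5 − 0.5 × 19 | 0 |

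**4. Power for 38 mm Hg on the mean of the two postoperative values, 36 per arm.**
- Unadjusted: SD = 70 × √((1 + 0.5)/2) = 60.62; SE = 60.62 × √(2/36) = 14.29; 38/14.29 = 2.66; power 0.75 (t)
- Change from presurgery: SD = 70 × √(0.75 + 1 − 2 × 0.5) = 60.62, so the same 0.75
- Presurgery OI as covariate: SD = 70 × √(0.75 − 0.5²) = 49.50; SE = 49.50 × √(2/36) = 11.67; 38/11.67 = 3.26; power about 0.89 (t)

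**The case against.** The strongest reply is that one loose verb is being made into a design flaw. Chance imbalance is part of the sampling variation that the test allows for. Over repeated trials it causes no bias and does not inflate the type I error. The 19 mm Hg threshold is a choice, and a gap as large as the full target is rare (1.5% for one pair). The SD of 70 is given for a single OI observation and not specifically for the presurgery value. All of this stands. The errors in step 3 are conditional on a gap having occurred, and they do not make the planned test invalid. What remains is that the sentence is wrong and that available precision is left unused.

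A reader might infer more from the text. Three stronger readings are not supported:

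- **That allocation is unrestricted, so arm sizes will drift from 40.** The article does not say this. A digit table can generate a blocked list, section 3.4.1 describes a balanced trial with "For a balanced 4-group trial, approximately 40 patients must be recruited per allocation group", and an article may leave block details to the full protocol. The sentence at issue concerns characteristics, not numbers.
- **That unequal arms would seriously weaken the trial.** Even under simple randomisation, mean pairwise power with 144 evaluable patients would be 0.797, against 0.805 at a fixed 36 per arm.
- **That randomisation should be stratified by presurgery OI.** Section 2.6.2 places a baseline assessment before randomisation but does not list OI in it, and the content of Table 1 is not shown. The text after the 100% xenon arm (2.9.3) calculates OI at set ventilator settings. The documents therefore do not show that this OI exists when the patient is randomised.

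**Conclusion.** The point holds as a wrong statement about what randomisation delivers, together with a missed use of presurgery OI. It is not a finding about arm sizes or about the form of the allocation list, and the planned total of 160 reproduces.

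The exposure is about a 48% chance that some xenon arm starts more than 19 mm Hg away from control, whether or not the arms are exactly equal. The gain from adjustment is power of about 0.89 instead of about 0.75 for the mean of the two postoperative values.

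Both figures assume an SD of 70 mm Hg at every time point. The power figures further assume a correlation of 0.5 between every pair of times and an effect of 38 mm Hg at both postoperative times. Section 4.1 reports that the effect in the earlier study had diminished by 6 hours; if that recurs, power falls under every one of these analyses. The covariate must also be measured before the allocated gas begins. Section 2.9.3 says OI is recorded before the operation, while sections 2.8 and 2.9 start the gas after intubation, so the order should be confirmed.

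**What to change.** 1. In 2.6.2, replace the claim that the table ensures balance with a statement that randomisation balances patient characteristics in expectation.
2. In 2.4.1 and 3.4.3, make OI at the end of surgery and at 6 hours the outcome measurements, and enter presurgery OI as a covariate in the repeated-measures model. Specify this before unblinding, whatever the baseline comparison shows.
3. State that presurgery OI is taken before the study gas starts.

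The cost is a few sentences and a changed model specification. No additional patients, measurements or changes to the allocation list are needed, and presurgery OI need not be known at randomisation. The sample size text should then be restated for the adjusted postoperative comparison. With 36 per arm, the plan's own inputs leave it above the 80% at which the trial was planned.

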#### Surgery

2.6.3

As a previous study described^[16]^ in brief, a stent graft and a 4-branch prosthetic graft will be used for arch replacement. Valve-sparing root resection (aortic valve plasty, the David procedure, or valsalva sinus plasty) or valve graft replacement will be performed according to the subtype of the aortic root.

#### Study assessments

2.6.4

Patients will complete their baseline assessments before surgery, and the remaining assessments are planned for the end of surgery, 6 and 24 hours postsurgery and 30-day postsurgery. Follow-up measurements will be conducted 3, 6, and 12 months after surgery.

### Study interventions

2.7

Patients randomized to surgery will remain unaware of which procedure they underwent (xenon or nitrogen). The study surgical procedures mirror each other, with standardized anesthesia, postoperative care, and rehabilitation for both groups. The patients will be mechanically ventilated with 50% to 100% oxygen and a 5-cm H_2_O positive end-expiratory pressure (PEEP). The end-tidal carbon dioxide pressure (P_ET_CO_2_) will be maintained at between 35 and 45 mm Hg by adjusting the tidal volume to 6 to 8 mL/kg with a respiratory rate of 10 to 15 times/min. Further details of the individual interventions are listed below.

### Nitrogen group (control group)

2.8

The nitrogen arm is the surgical comparison group. The procedure will be performed while the patient is under general anesthesia. After routine intubation, 50% nitrogen/50% oxygen will be inhaled for 1 hour, and then 100% oxygen continued until cardiopulmonary bypass (CPB) is performed. After the aorta is cross-clamped and mechanical ventilation stopped, the lungs will be inflated with 50% nitrogen/50% oxygen to maintain a mean airway pressure. Pulmonary static inflation will be stopped 15 minutes before aortic declamping and cardiac resuscitation. One hour after the end of CPB, 50% nitrogen/50% oxygen will be inhaled for 1 hour, and then 100% oxygen will be continued until the end of surgery. These measures provide the oxygen group with the characteristics necessary to provide a reasonable comparison and to account for the placebo effects of surgery.

### Xenon group

2.9

The procedure will be performed with the patient under general anesthesia. After routine intubation, 50% xenon/50% oxygen will be inhaled for 1 hour, and then 100% oxygen continued until CPB is performed. One hour after the end of CPB, 50% xenon/50% oxygen will be inhaled for 1 hour, and then 100% oxygen will be continued until the end of surgery.

#### 50% xenon group:

2.9.1

After the aorta is cross-clamped and mechanical ventilation is stopped, the lungs will be inflated with 50% xenon/50% oxygen to maintain a mean airway pressure. Pulmonary static inflation will be stopped 15 minutes before aortic declamping and cardiac resuscitation.

#### 75% xenon group:

2.9.2

After the aorta is cross-clamped and mechanical ventilation stopped, the lungs will be inflated with 75% xenon/25% oxygen to maintain a mean airway pressure. Pulmonary static inflation will be stopped 15 minutes before aortic declamping and cardiac resuscitation.

#### 100% xenon group:

2.9.3

After the aorta is cross-clamped and mechanical ventilation stopped, the lungs will be inflated with 100% xenon to maintain a mean airway pressure. Pulmonary static inflation will be stopped 15 minutes before aortic declamping and cardiac resuscitation.

The OI will be recorded before the operation, at end of surgery, and 6 hours postoperatively. OI will be calculated based on an FiO_2_ of 100%, a PEEP of 5 cm H_2_O, a tidal volume of 8 mL/kg, an inspiratory/expiratory ratio of 1:2, and a respiratory rate of 10 times per minute.

## Safety

3

Data on complications will be recorded as outcomes, and the severity and frequency of all complications will be assessed and reported.

### Definition of serious adverse events

3.1

A serious adverse event (SAE) is any negative medical occurrence, including death, life-threatening injury, an change requiring inpatient hospitalization or prolongation of existing hospitalization or a change that results in persistent or significant disability and/or incapacity.

### Reporting procedures for unexpected serious adverse events

3.2

All unexpected serious adverse event (USAE), related to any of the research procedures or not listed in the protocol, will be reported to the Beijing Anzhen Hospital Clinical Research Ethics Committee that will issue a favorable opinion of the study and compensate to those who suffer harm from trial participation. Reports of related SAEs and USAEs should be submitted within 24 hours of the principal investigators awareness of the event.

### Follow-up and end of study definition

3.3

After 3, 6, or 12 months, the participant will be consulted in out-patient department or contacted by telephone for assessment of individual survival, living condition, and major adverse events. The whole duration of the study will be 1 year and will end after the 1-year follow-up of the last patients. Participants have no obligation to complete the whole study and they are free to decide to withdraw at any point.

